# Rationale and design of the Sodium Lowering In Dialysate (SoLID) trial: a randomised controlled trial of low versus standard dialysate sodium concentration during hemodialysis for regression of left ventricular mass

**DOI:** 10.1186/1471-2369-14-149

**Published:** 2013-07-15

**Keywords:** Home hemodialysis, Dialysis, Left ventricular mass, Sodium, Blood pressure, Fluid overload, Dialysate

## Abstract

**Background:**

The current literature recognises that left ventricular hypertrophy makes a key contribution to the high rate of premature cardiovascular mortality in dialysis patients. Determining how we might intervene to ameliorate left ventricular hypertrophy in dialysis populations has become a research priority. Reducing sodium exposure through lower dialysate sodium may be a promising intervention in this regard. However there is clinical equipoise around this intervention because the benefit has not yet been demonstrated in a robust prospective clinical trial, and several observational studies have suggested sodium lowering interventions may be deleterious in some dialysis patients.

**Methods/design:**

The Sodium Lowering in Dialysate (SoLID) study is funded by the Health Research Council of New Zealand. It is a multi-centre, prospective, randomised, single-blind (outcomes assessor), controlled parallel assignment 3-year clinical trial. The SoLID study is designed to study what impact low dialysate sodium has upon cardiovascular risk in dialysis patients. The study intends to enrol 118 home hemodialysis patients from 6 sites in New Zealand over 24 months and follow up each participant over 12 months. Key exclusion criteria are: patients who dialyse more frequently than 3.5 times per week, pre-dialysis serum sodium of <135 mM, and maintenance hemodiafiltration. In addition, some medical conditions, treatments or participation in other dialysis trials, which contraindicate the SoLID study intervention or confound its effects, will be exclusion criteria. The intervention and control groups will be dialysed using dialysate sodium 135 mM and 140 mM respectively, for 12 months. The primary outcome measure is left ventricular mass index, as measured by cardiac magnetic resonance imaging, after 12 months of intervention. Eleven or more secondary outcomes will be studied in an attempt to better understand the physiologic and clinical mechanisms by which lower dialysate sodium alters the primary end point.

**Discussion:**

The SoLID study is designed to clarify the effect of low dialysate sodium upon the cardiovascular outcomes of dialysis patients. The study results will provide much needed information about the efficacy of a cost effective, economically sustainable solution to a condition which is curtailing the lives of so many dialysis patients.

**Trial registration:**

Australian and New Zealand Clinical Trials Registry number: ACTRN12611000975998

## Background

Dialysis is the world’s most utilized modality of renal replacement therapy [1], and enables patients with end stage kidney disease (ESKD) to avoid imminently fatal complications such as hyperkalemia, acidosis, and pulmonary edema and thereby live longer. However, it is apparent that those on dialysis continue to have a uremic toxicity as manifested by a high rate of premature mortality. As is the case in other countries, the median survival of dialysis patients in New Zealand is approximately 4 years, with an overall mortality rate several-fold higher than that of the general population (Figure 1) [2]. This situation is largely attributable to premature cardiovascular (CV) death, with infection playing the next most important role. Although not commonly appreciated, the patients with the highest proportion of CV deaths are those on home hemodialysis (HD), probably as a result of a lower competing risk of infectious death due to patient selection and reduced exposure to nosocomial pathogens. In Australia and New Zealand, 67% of patients on home HD die from CV disease [3].

**Figure 1 F1:**
[figure not shown]
Mortality in New Zealand patients treated by dialysis and transplantation during 2010 compared to the New Zealand general population.

The mechanism of CV death in dialysis patients appears to be different from that in the general population. Sudden cardiac death (SCD) due to lethal arrhythmia accounts for approximately half of CV deaths in the general population, and is most often a manifestation of coronary heart disease [4]. In contrast, SCD accounts for the majority of CV deaths in dialysis patients and is probably less likely due to sudden coronary ischemia [5,6]. More likely, arrhythmogenesis is triggered by re-entry pathways that are superimposed upon the usual ventricular conducting system by inter-myocardial cell fibrosis [7-9]. This fibrosis results from a synergy between left ventricular (LV) hypertrophy and uremia per se [10,11], and also contributes to a stiff and impaired myocardium and ultimately congestive heart failure [12-16].

There is a range of clinical evidence that supports the crucial role of for LV hypertrophy in SCD among dialysis patients. In a multitude of studies, the presence of LV hypertrophy is a strong independent mortality risk. In a landmark study, LV hypertrophy was associated with a relative risk for death of 2.9, even when adjusted for age, known coronary artery disease, diabetes, and blood pressure (BP) [17]. Of equal importance, recent studies have demonstrated that that the effect of lipid lowering therapy is attenuated in patients with kidney disease, reinforcing the lesser role of sudden rupture of lipid rich plaques as a mechanism of SCD in this group [18-21]. On balance, LV hypertrophy is regarded as a prime and causal risk factor for SCD, and the regression of LV hypertrophy accepted as a validated surrogate primary end point for interventions aiming to reduce CV mortality in dialysis patients [12,22,23].

Persistently elevated blood pressure (BP) and extra-cellular fluid (ECF) overload due to positive salt and water balance are significant contributors to on-going LV hypertrophy with conventional (non-extended-hours) dialysis [24-33]. Current methods to control these factors with either drug therapy or ultra-filtration in patients on conventional dialysis can be effective but are often inadequate in routine clinical practice [27,34-38]. The most effective intervention to improve LV hypertrophy is extended-hours or frequent HD. A randomised controlled trial of extended-hours HD demonstrated a 7.7% reduction in LV mass over a 6month period for patients dialysed in this manner, as opposed to a stable LV mass in those dialysed conventionally [35]. Similar findings were published in the Frequent Haemodialysis Network trial [34]. In both studies, regression of LV mass was associated with improved measures of BP and ECF volume control. Several observational studies have reported similar findings [39,40].

Not all patients, however, are able to manage extended-hours or frequent HD and not all health systems are able to deliver such programs. A more accessible alternative may be available in reducing sodium exposure through lower dialysate [Na+]. Sodium loading by either excessive dietary intake or excessive diffusion via dialysate has been shown to increase both BP and intra-dialytic weight gain (IDWG) [41]. Moreover, elevation in plasma [Na+] can induce hypertension independently of EC fluid volume, through mechanisms that probably include stiffening of vascular endothelium [42-46]. A number of observational studies as well as small and often uncontrolled clinical studies have shown that lower dialysate [Na+] associates with less thirst [47-55], lower IDWG [48,49,51-53,56-78], lower ECF volume [66,76,79,80], and lower BP [48,51,54,56,61-69,75,81-83], with only a minority of studies being completely negative [47,77,84-88]. A typical example can be found in preliminary research by the SoLID trial research team, who previously showed that a decrease in dialysate [Na+] by 3 mM in 52 facility based patients was well tolerated and reduced systolic and diastolic BP by 4–5 and 2–3 mmHg, respectively [89]. Improvement in intermediary outcomes such as BP suggest that lower dialysate [Na+] could be beneficial for improving LV hypertrophy as well. There have been only two studies examining the effect of lower dialysate [Na+] on LV structure and function [90,91]. One study reported an associated decrease in LV volumes, although both were too brief to assess for changes in LV mass.

However, the potential benefits of lower dialysate [Na+] should be weighed against a potential “dark side”. Several large and well performed observational analyses have shown an association between lower dialysate [Na+] and higher mortality risk, notably in those patients with a “frail” phenotype characterized by low serum [Na+], diabetes mellitus, coronary artery disease, CV disease, congestive heart failure, cerebrovascular disease, lung disease, and cancer [72,92,93]. The most plausible explanation for these observations relates to decreased hemodynamic stability with lower dialysate [Na+], and the vulnerability of “frail” patients to intra-dialytic hypotension, an unquestionably threatening condition associated with myocardial stunning and all-cause patient mortality [94-99]. Intra-dialytic hypotension is ameliorated by higher dialysate [Na+], and is likely to be at least as deleterious (if not more so) as inter-dialytic hypertension.

Another concern with lower dialysate [Na+] is that it might influence serum [Na+]. Humans are considered to have an individual natremic set point, and most observational studies have not shown any cross-sectional correlation between dialysate and serum [Na+] [67,73,100-105]. However, pre-dialysis serum [Na+] did change in several small prospective clinical trials after changes to dialysate [Na+] [54,58,62,64,89,106,107], albeit often after a lag of several months possibly due to the large reservoirs of non-osmotic sodium in skin and bone [108-111]. There is a clear association between low serum [Na+] and patient mortality in patients with kidney disease, and an intervention that might potentially lower serum [Na+] warrants careful scrutiny [112-114].

A final concern is raised by clinical trials of dietary salt reduction in non-ESKD populations. Overall, there is higher mortality and morbidity in those participants who had the lowest salt intake, especially in the setting of generally low salt consumption [115-117]. A number of plausible biological mechanisms might be contributing to the poorer outcomes among those with low salt intake, involving several key metabolic and neurohormonal pathways (e.g. activation of sympathetic nervous and renin–angiotensin systems, increased in total and low-density lipoprotein cholesterol, reduction in peripheral insulin sensitivity etc.) [118-121].

Overall, there is clinical equipoise around lower dialysate [Na+] due to the multiple physiological consequences of reducing salt exposure in this population, and the uncertain net effect on CV outcomes as a result of these often competing and often conflicting physiological responses (Figure 2) [41]. The SOdium Lowering In Dialysate (SoLID) trial has been designed to answer the following clinical question: Does lower dialysate [Na+] improve CV mortality risk compared to conventional dialysate [Na+], in prevalent home HD patients who are exposed over a duration of a year? The research aims to address the clinical question through a randomised controlled trial of low versus standard dialysate [Na+], while observing the effect of allocation and exposure upon participant’s LV mass, an accepted surrogate outcome for CV mortality in end-stage kidney disease populations [12,22,23,36,122].

**Figure 2 F2:**
[figure not shown]
**Causal diagram relating low salt exposure during hemodialysis to cardiovascular mortality risk (reproduced with permission from Marshall and Dunlop **[41]**).**

## Methods/design

### Study aim and hypothesis

The aim of this research is to examine the impact of low dialysate [Na+] on cardiovascular risk in patients on dialysis. Our primary hypothesis is that low dialysate [Na+] for one year among patients undergoing home HD will result in reduced LV mass. Our secondary hypothesis is that low dialysate [Na+] will also result in the following outcomes compared to conventional dialysate [Na+]: improved markers of thirst; better control of BP and markers of ECF volume; improved LV volumes and hemodynamics; decreased arterial stiffness; improved markers on long term CV mortality risk; non-inferior tolerance to dialysis; non-inferior plasma Na+ ionic activity and osmolarity; and non-inferior health-related quality of life.

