### Analysis populations

For analysis of data, we define Intention to Treat (ITT) and Per Protocol (PP) populations. The ITT population consists of all randomised participants who have at least one baseline measurement, and is the primary population of interest. All randomised participants will be analysed in the group they were allocated to, even if they do not receive the allocated treatment, do not commence treatment, change dialysis modality, are lost to follow-up, or die thereby preserving the intention-to-treat framework. In particular, titration failures will remain within the ITT population as participants.

The PP population consists of participants that fulfil criteria for the ITT population, have complete primary endpoint measurements and do not present any major protocol violations during the study. The following describes the major protocol deviations that will exclude patients from the PP population (minor deviations will not do so): eligibility violation; absence of any efficacy data, titration failure; other major violations will be identified by the DMC of the trial during the study and/or during the data review process. The list of all protocol deviations will be reviewed by the DMC who will determine the degree of the violation (i.e. major versus minor). All protocol deviations considered as minor will not lead to excluding patients from the PP population for analysis.

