Tolerability	ITT	None	Hypotension event counts	Multivariate, mixed effects, allowing for treatment time interaction

Abbreviations: *PP* per protocol, *ITT* intention to treat, *LVMI* left ventricular mass index, *FDR* False Discovery Rate.

All tests of significance of hypotheses concerning treatment effect parameters will be carried out using a level of significance of 5% and two-sided alternatives. The significance threshold of potential covariates will be set at 10%, to promote unbiased and conservative inference. All estimates will be produced as point estimates and as 95% confidence intervals. Unless otherwise noted, model selection when required will be performed using backward selection from the largest model dictated by the situation. Per comparison error rate (PCER) control will be used in all analyses, with the exception of some subgroup analyses where False Discovery Rate (FDR) control will be implemented.

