### Secondary outcomes

For all secondary outcomes other than health-related quality of life, we will undertake multivariate (repeated outcomes) endpoint analysis. For health-related quality of life, we will use univariate analyses in a manner similar to that presented for the primary outcome. Otherwise, analyses will fit all outcomes as repeated measures over the 2–4 assessment time points to an appropriate regression model using generalised estimating equations (GEEs). Changes from baseline will be associated with the assessment time (from baseline), the treatment arm, and the interaction of the two, adjusting for baseline and potentially for other confounding covariates, if applicable, similarly to the procedure outlined above for the primary outcome. The procedure will account for clustering on subjects; independent, exchangeable and autoregressive working correlation structures will be used and the best option in terms of Quasilikelihood Information Criterion retained for the final analyses [176]. Time-averaged analyses will be implemented by appropriately weighting each observation, accounting for any missing time point, so as to produce inference on the estimated average value over the available individual follow-up period. All results will be estimates of treatment effect and treatment-time interaction contrasts. Results will be reported as the point estimates and 95% confidence intervals for these quantities.

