### Tolerability analysis

Tolerability of dialysis will be compared between the two arms by assessing the frequency of intra-dialytic hypotension episodes using negative binomial regression of the number of events as dependent variable and the logarithm of the duration of the period covered (normally two weeks, prior to assessment). To identify any effect of prolonged exposure to the treatment, the dependent variable will be similarly modelled as a repeated measure on the time of assessment, the treatment arm and their interaction. To maintain interpretability at the patient level, conditional (mixed effects) rather than marginal (GEE) methodology will be used to estimate tolerability trends. Normally distributed random effects will account for the baseline dialysis tolerance in each participant. The treatment and treatment interaction contrasts from the tolerability analyses will be reported as point estimates and 95% confidence intervals.

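### Three secondary hypotheses are worded as non-inferiority, but the stated rule is a two-sided 5% test with no margin or confidence-limit criterion

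*Protocol article*

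**What the plan says.** Under Study aim and hypothesis, most secondary hypotheses predict an improvement. Three do not; they predict "non-inferior tolerance to dialysis; non-inferior plasma Na+ ionic activity and osmolarity; and non-inferior health-related quality of life". The term non-inferior appears nowhere else in the article.

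The Statistical analysis section, in the text after Table 2, sets the testing rule: "All tests of significance of hypotheses concerning treatment effect parameters will be carried out using a level of significance of 5% and two-sided alternatives". No exception is made for non-inferiority. The same paragraph adds: "All estimates will be produced as point estimates and as 95% confidence intervals".

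The analyses of the three outcomes are:

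- **Quality of life** (Secondary outcomes): "For health-related quality of life, we will use univariate analyses in a manner similar to that presented for the primary outcome". That is ANCOVA with a point estimate and 95% interval.
- **Plasma sodium activity and osmolality** (Secondary outcomes): GEE on change from baseline. "All results will be estimates of treatment effect and treatment-time interaction contrasts", again with 95% intervals.
- **Tolerance** (Tolerability analysis): "Tolerability of dialysis will be compared between the two arms by assessing the frequency of intra-dialytic hypotension episodes", by negative binomial regression and a mixed model. "The treatment and treatment interaction contrasts from the tolerability analyses will be reported as point estimates and 95% confidence intervals".

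On populations, "The ITT population consists of all randomised participants who have at least one baseline measurement, and is the primary population of interest". Table 2 lists the per-protocol set for the primary endpoint only. The Power calculation covers LVMI only.

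**The concern.** A non-inferiority hypothesis says that the new treatment is worse by less than a stated amount. A two-sided test of no difference does not address that. If it is significant, it shows a difference. If it is not, it leaves open how large a difference could still be present. Without a margin, non-inferior has no numerical meaning.

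These outcomes carry the harm side of the trial's equipoise. The Background treats intra-dialytic hypotension as a serious threat and asks for careful scrutiny of anything that may lower serum sodium. It also reports that pre-dialysis serum sodium did change in several small prospective trials after dialysate sodium was changed. If some fall is plausible, the question is how much fall is acceptable, and the hypothesis does not say. The risk is that a statement of acceptable tolerance or stable sodium ends up resting on a non-significant p-value from a trial sized for another outcome.

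**Working it through.** **1. The plan's own sample size, to fix the number evaluable.** Inputs from Power calculation: baseline LVMI 110 (SD 40), 12-month LVMI 95 (SD 35) in the low-sodium arm, correlation 0.75, power 0.8, alpha 0.05, 25% dropout. The control arm's 12-month value is not stated; I assume it stays at 110 (40), so the difference is 15.

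n = (1.960 + 0.842)² × (40² + 35²) × (1 − 0.75²) / 15² = 43.1, so 44 per arm. Then 44 / 0.75 = 58.7, so 59 per arm. The stated figure reproduces. It gives power for LVMI only.

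**2. What a non-significant result would mean for a continuous outcome.** The article gives no SDs for plasma sodium, osmolality or quality of life, so I work in SD units over a range of baseline correlations ρ (assumed). With 44 per arm, SE = √(2(1 − ρ²)/44). The 95% half-width is 1.96 × SE. If the low-sodium arm is truly worse by x, the chance of p > 0.05 is about Φ(1.96 − x/SE).

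| ρ | SE | 95% half-width | P(p > 0.05), x = 0.3 SD | P(p > 0.05), x = 0.5 SD |
|---|---|---|---|---|
| 0 | 0.213 | 0.42 SD | 71% | 35% |
| 0.5 | 0.185 | 0.36 SD | 63% | 23% |
| 0.75 | 0.141 | 0.28 SD | 43% | 6% |

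**3. Hypotension.** The article gives no event rate or dispersion. I assume μ = 1 to 4 episodes per participant over the counted windows, dispersion k = 0.5 to 2, and 44 completers per arm. SE(log rate ratio) = √(2(1/μ + k)/44), and the 95% interval extends by a factor exp(1.96 × SE) either side.

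| μ | k | SE | Factor |
|---|---|---|---|
| 4 | 0.5 | 0.185 | 1.44 |
| 2 | 1 | 0.261 | 1.67 |
| 1 | 1 | 0.302 | 1.81 |
| 1 | 2 | 0.369 | 2.06 |

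An observed ratio of exactly 1.0 would have an upper limit of 1.44 to 2.06, that is, a 44% to 106% excess.

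**4. What the planned intervals could support.** Comparing one limit of a two-sided 95% interval with a margin is a one-sided 2.5% non-inferiority test. With a true difference of 0 and 44 per arm, the smallest margin with 80% power is (1.960 + 0.842) × SE: 0.60 SD (ρ = 0), 0.52 SD (ρ = 0.5) or 0.40 SD (ρ = 0.75). At a margin of 0.3 SD the power is 29%, 37% or 57%. The models and intervals are usable; the conclusion depends on a margin that the article does not give.

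**The case against.** The strongest reply is that this is a condensed article and that margins for unpowered secondary outcomes belong in the full protocol or analysis plan. For the margin alone that would be fair. But the article goes further: it states the hypotheses and fixes one testing rule for all of them, and that rule does not fit three of them.

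A reader might infer several stronger things, which the document does not support:

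- *That the planned analyses cannot establish non-inferiority.* The planned 95% intervals can, once a margin is fixed.
- *That the investigators will read non-significance as non-inferiority.* The article nowhere says so.
- *That dropouts in the intention-to-treat set pull the arms together.* Under Missing data, an absent outcome removes that participant and time point, so it adds no diluting data. Dilution can come only from people measured away from their allocated level, such as titration failures.
- *That a per-protocol analysis must agree before non-inferiority is claimed.* The per-protocol set excludes titration failures and participants without complete primary endpoint data. If titration fails through intolerance, that set removes the people who show the harm.

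The hypotension figures are also open to challenge. The rates and dispersion are assumed, and the formula uses one total per completer, whereas the plan models repeated counts with participant random effects and keeps the visits of people who later drop out. They are an illustration of scale. Finally, a Data Monitoring Committee reviews safety every six months, so a gross excess of harm need not wait for the final analysis. That does not supply a criterion for the final claim.

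**Conclusion.** The point holds in this form: the hypotheses on tolerance, plasma sodium activity and osmolality, and quality of life are stated as non-inferiority, while the only stated testing rule is a two-sided 5% test with no margin or confidence-limit criterion. That rule cannot by itself support the hypotheses, and non-significance would not show non-inferiority. The mismatch needs no assumption. Its possible size does: the 43% to 71% chance of missing a 0.3 SD deficit rests on 44 evaluable per arm and the assumed correlations, and the rate-ratio factors of 1.44 to 2.06 rest on the assumed event rates and dispersion.

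Severity is moderate. These are unpowered secondary outcomes, and the primary LVMI hypothesis, sample size and analysis are unaffected.

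**What to change.** Before allocation and outcomes are merged, do one of the following:

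1. For each of the three outcomes, name the score or contrast concerned, the adverse direction and a justified margin (a rate-ratio margin for hypotension). Claim non-inferiority only if the relevant limit of the two-sided 95% interval excludes the margin.
2. Delete non-inferior from the secondary hypothesis and report these outcomes as estimates with 95% intervals, as the plan already provides.

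In either case, state that a non-significant difference is not evidence of non-inferiority. Keep intention to treat as the main analysis. If a per-protocol run is added, label it a sensitivity analysis and note that excluding titration failures may remove participants who did not tolerate their allocation.

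The cost is a few sentences, plus the work of justifying margins under option 1; neither option needs more participants or data. The downside of option 1 is that non-inferiority may well not be shown, because the trial was not sized for these outcomes.
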